#### Duration of treatment and follow-up

2.4.3

The study intervention will be discontinued 7 days after randomization, discharge from the study ICU, death or cessation of gastric feeding, whichever comes first. All randomized patients will be followed for 28 days after randomization, unless death occurs earlier. For patients who remain hospitalized on study day 28, follow-up will be censored at day 28, and all outcomes will be recorded at that time point.

#### Trial termination and intervention discontinuation

2.4.4

Participants may withdraw from the study at any time and for any reason, without any impact on their current or future clinical care provided by the investigators or treating clinicians. Investigators are required to document the reason(s) for withdrawal. The extent of withdrawal (e.g., discontinuation of study intervention, termination of active study participation, or cessation of all study-related contact) will be recorded in the electronic Case Report Form (eCRF). Post-randomization follow-up of withdrawn participants will be pursued to the extent permitted by participant consent. If consent is provided, follow-up assessments may be conducted by telephone.

The study intervention (pectin) will be immediately discontinued under any of the following circumstances:

1. Occurrence of a serious adverse event (SAE) or a concurrent medical condition for which continuation of pectin is considered not to be in the participant’s best interest, as judged by the investigator.

2. Withdrawal of informed consent by the participant.

The reason(s) and date(s) for intervention discontinuation or study withdrawal will be documented in the eCRF. If pectin is discontinued due to an SAE, safety monitoring will continue until the event has resolved or stabilized, or until it is determined to be unrelated to the study intervention. All relevant adverse events will be formally recorded in accordance with study procedures.

### Data collection and management

2.5

Data will be collected and stored using a secure, web-based electronic data capture system (Unimed Science Inc., Wuxi, China). At each participating center, the principal investigator will be responsible for oversight of patient enrollment and data entry. Data entry will be performed exclusively by the principal investigator or by up to two designated research staff members authorized by the principal investigator.

Standardized training in data entry and database use will be provided by the database vendor in collaboration with the CCCNTG coordinating center. All data required to characterize baseline patient characteristics (Table 1), study and control interventions, potential confounding co-interventions, and study outcomes will be systematically and prospectively collected in accordance with the study protocol. Table 2 shows the schedule of enrolment, interventions, and main data collected.

**TABLE 1 T1:** Baseline characteristics of patients by treatment group.

Characteristics	Pectin group (*n* = xx)	Control group (*n* = xx)
Age, years		
Male gender, no. (%)		
BMI, kg/m^2^		
Admission diagnosis, no. (%)		
Respiratory		
Cardiovascular		
Gastrointestinal		
Neurological		
Sepsis		
Trauma		
Others		
ICU source of admission, no. (%)		
Emergency		
Medical		
Surgical		
Others		
Comorbidities, no. (%)		
Hypertension		
Coronary disease		
Diabetes		
Chronic respiratory diseases		
Stroke		
Gastrointestinal disease		
Malignant tumor		
Others		
Interval from ICU admission to randomization, days		
APACHE II score		
SOFA score		
mNUTRIC score		
Presence of organ failure at baseline, no. (%)		
Respiratory		
Renal		
Cardiovascular		
Organ support at baseline, no. (%)		
Renal replacement therapy		
Vasoactive drugs		
Serum albumin, g/L		
Serum creatinine, μmol/L		
BUN, mmol/L		
CRP, mg/L		
PPIs use before randomization, no. (%)		

BMI, body mass index; ICU, intensive care unit; APACHE II, Acute Physiology and Chronic Health Evaluation II; SOFA, Sequential Organ Failure Assessment; mNUTRIC, modified Nutrition Risk in the Critically Ill; BUN, blood urea nitrogen; CRP, C-reactive protein; PPI, proton pump inhibitor.

**TABLE 2 T2:** Schedule of enrolment, intervention, and data collection.

	Study period									
Time point	Screening	Randomiza-tion	After randomization/day							End
		0	1	2	3	4	5	6	7	28
Enrollment										
Eligibility screen	×	–	–	–	–	–	–	–	–	–
Informed consent	×	–	–	–	–	–	–	–	–	–
Allocation	–	×	–	–	–	–	–	–	–	–
Intervention										
Intervention group	–	×	×	×	×	×	×	×	×	–
Control group	–	×	×	×	×	×	×	×	×	–
Assessments										
Baseline characteristics	×	×	–	–	–	–	–	–	–	–
Laboratory parameters	–	–	×	×	×	×	×	×	×	–
APACHE II score	–	–	×	×	×	×	×	×	×	–
SOFA score	–	–	×	×	×	×	×	×	×	–
mNUTRIC score	–	–	×	×	×	×	×	×	×	–
Feeding Intolerance Score (FIS)	–	–	×	×	×	×	×	×	×	–
Gastrointestinal Dysfunction Score (GIDS)	–	–	×	×	×	×	×	×	×	–
Bristol stool score	–	–	×	×	×	×	×	×	×	–
Daily energy intake	–	–	×	×	×	×	×	×	×	–
Daily protein intake	–	–	×	×	×	×	×	×	×	–
Caloric adequacy	–	–	–	–	×	–	×	–	×	–
Protein adequacy	–	–	–	–	×	–	×	–	×	–
New-onset organ failure	–	–	×	×	×	×	×	×	×	–
Receipt of organ support	–	–	×	×	×	×	×	×	×	–
Clinical outcomes	–	–	–	–	–	–	–	–	–	×
Adverse events	–	–	×	×	×	×	×	×	×	×

APACHE II, Acute Physiology and Chronic Health Evaluation II; SOFA, Sequential Organ Failure Assessment; mNUTRIC, modified Nutrition Risk in the Critically Ill.

### Sample size estimation

2.6

Based on a previous nationwide multicenter trial (the NEED trial) conducted by the CCCNTG (19), among patients receiving invasive mechanical ventilation, the mean (standard deviation) ratio of EN energy intake to the prescribed target energy on Day 5 was 62.9% (31.1%) in the control group. Assuming a minimal clinically meaningful relative increase of 20% in the intervention group, with 80% power, a two-sided alpha of 0.05, and a 1:1 allocation ratio, the required sample size is 96 participants per arm (PASS ver.11.0; NCSS, LLC). To account for potential attrition, including withdrawal or dropped, estimated at approximately 10%, the final sample size was increased to 212 participants (106 per group).

### Data analysis

2.7

Reporting and presentation of trial results will adhere to the Consolidated Standards of Reporting Trials (CONSORT) guidelines (22). The primary analysis will be conducted according to the intention-to-treat (ITT) principle, with secondary supportive analyses performed in the per-protocol (PP) population and safety analyses in the safety population.

Analysis populations are defined as follows. The ITT population comprises all randomized participants. The PP population comprises participants who completed the intervention in accordance with the study protocol, excluding those with major protocol deviations, defined as: (a) enrollment of participants subsequently confirmed ineligible; (b) receipt of <80% of the planned pectin dose. All deviations will be prospectively recorded in a Protocol Deviation Log in the eCRF and reviewed by the TMC at each monitoring visit. The safety population comprises all participants who received at least one dose of the study intervention.

Primary outcome analysis: Patients who die before Day 5 are excluded from the primary analysis as a pre-specified competing event. A sensitivity analysis will assign these patients an EN delivery ratio of 0% (worst-case assumption), reported alongside the primary complete-case analysis. Administratively missing primary outcome data are anticipated to be <5% based on prior NEED trial experience (19) and will be handled by complete-case analysis with transparent reporting of the missing data rate. The number of deaths before Day 5 in each arm will be reported in the CONSORT flow diagram and primary analysis table to ensure full ITT accounting.

Time-to-event analyses: A competing risks framework using the Fine-Gray subdistribution hazard model, with death as the competing event, will be applied to time-to-event outcomes including time to achieve ≥ 80% of the prescribed EN target, time to ICU discharge, and time to hospital discharge, etc. Kaplan-Meier curves for 28-day mortality will be presented for both groups with log-rank comparison.

Statistical methods: Normality of continuous variables will be assessed using the Shapiro-Wilk test. Normally distributed continuous variables will be summarized as mean ± standard deviation and compared using Student’s *t*-test; non-normally distributed variables will be summarized as median (interquartile range, IQR) and compared using the Mann-Whitney U test. Categorical variables will be summarized as counts and percentages and compared using Pearson’s chi-square test. Effect estimates with 95% confidence intervals (CIs) will be reported throughout. No adjustment for multiple comparisons will be applied; all secondary outcome analyses are considered exploratory and hypothesis-generating. For secondary outcomes, complete-case analysis will be used, with missing data rates reported for each outcome. A two-sided *P*-value < 0.05 will be considered statistically significant.

Subgroup analyses: Pre-specified subgroup analyses will be conducted according to the following baseline characteristics: age (>60 vs. ≤59 years), BMI (>25 vs. ≤25 kg/m^2^), SOFA score (≥9 vs. <9), and ICU admission type (emergency, surgical, medical, or other).

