### Randomization and blinding

2.2

The randomization sequence will be generated by an independent statistician using SAS Version 9.4 with a fixed block size of 4, ensuring allocation in a 1:1 ratio. Randomization will be stratified by study site. Allocation concealment will be ensured through a secure, encrypted, password-protected central web-based randomization system.^1^

Blinding of participants and treating clinicians was not feasible because pectin supplementation changes the handling and administration characteristics of the enteral formula, making it distinguishable from standard care during routine clinical practice. No placebo will be provided to the control group. Nonetheless, outcome assessors and data analysts will remain blinded to group assignments to minimize assessment and analytic bias.

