#### Control group

2.3.2

The comparator will be usual nutritional care, delivered and managed in accordance with the CCCNTG feeding protocol^2^ based on international guidelines (19).

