### Adverse events

2.9

Adverse events (AEs) are defined as any unfavorable medical occurrence in a study participant receiving the investigational intervention, regardless of its causal relationship to the intervention, in accordance with the National Cancer Institute Common Terminology Criteria for Adverse Events (NCI-CTCAE v5.0) (23).

Given the severity of underlying illness in critically ill patients, abnormalities in laboratory values, signs, or symptoms are common and will not automatically be classified as AEs unless they require clinically significant intervention or are considered clinically relevant at the investigator’s discretion. The underlying condition or diagnosis should be documented whenever possible (e.g., “acute kidney injury” rather than “hyperkalemia”).

AE assessment follows a two-level framework: (1) all-cause AE grading using NCI-CTCAE v5.0; and (2) the following pectin-specific adverse events of interest, which will be actively monitored throughout the intervention period:

a. Abdominal distension: clinical diagnosis based on physical examination and/or intra-abdominal pressure (IAP) ≥ 12 mmHg on routine bladder pressure measurement, corresponding to Grade I intra-abdominal hypertension (IAH) per the World Society of the Abdominal Compartment Syndrome (WSACS) consensus (24).

b. Enteral tube obstruction: inability to aspirate gastric contents or flush the tube with 20 mL warm water, necessitating tube replacement or unplanned cessation of enteral feeding.

c. Ileus: absence of bowel sounds on ≥3 consecutive assessments combined with cessation of stool passage and abdominal distension in the absence of mechanical obstruction, requiring clinical intervention.

d. Intestinal ischemia: radiologically or surgically confirmed bowel ischemia, or strong clinical suspicion based on rising lactate and unexplained hemodynamic deterioration, prompting urgent computed tomography (CT) evaluation. Classified as SAE with mandatory immediate DSMB notification.

e. Aspiration pneumonia: new radiological infiltrates consistent with aspiration pneumonia occurring within 24 h of pectin administration and judged by the investigator as potentially related to altered gastric viscosity.

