Causality will be assessed by the site investigator using the WHO five-category classification (Certain/Probable/Possible/Unlikely/Unrelated); events judged Possible or above are included in the safety analysis. A SAE is defined as any event resulting in death, life-threatening condition, prolonged hospitalization, or persistent significant disability. Non-serious AEs will be documented in the eCRF within 24 h of detection. SAEs will be reported to the ethics committee and DSMB in accordance with regulatory requirements.

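### As worded, the safety rules leave the control arm out of the formal adverse-event analysis, so AE and SAE rates cannot be compared between arms

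*Protocol article*

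**What the plan says.** Section 2.7 (Data analysis) places the "safety analyses in the safety population" and defines that set: "The safety population comprises all participants who received at least one dose of the study intervention". Section 2.4.4 shows what the term means: "The study intervention (pectin) will be immediately discontinued under any of the following circumstances". The control arm has no equivalent exposure. Section 2.3.2 states: "The comparator will be usual nutritional care, delivered and managed in accordance with the CCCNTG feeding protocol". Section 2.2 adds: "No placebo will be provided to the control group".

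Section 2.9 (Adverse events) contains three further rules:

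- An AE is "any unfavorable medical occurrence in a study participant receiving the investigational intervention", whatever its causal relationship to the intervention.
- Aspiration pneumonia, event of interest (e), requires new infiltrates "occurring within 24 h of pectin administration and judged by the investigator as potentially related to altered gastric viscosity".
- After the site investigator has rated causality, "events judged Possible or above are included in the safety analysis".

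The same section also plans all-cause grading by CTCAE. It defines events of interest (a) to (d), namely distension, tube obstruction, ileus and intestinal ischaemia, without mentioning pectin exposure.

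**The concern.** Distension, ileus, aspiration and bowel ischaemia can arise in ventilated, tube-fed patients from the illness and from feeding itself. Section 2.9 accepts that abnormal signs and laboratory values are common in this population. A count of such events in treated patients alone cannot be interpreted without a control count made by the same rules.

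The gap hides benefit as well as harm. The introduction proposes reduced reflux and aspiration as an effect of pectin, yet aspiration pneumonia is defined so that no patient without pectin can have it.

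The relatedness rule adds an internal conflict. One sentence of section 2.9 makes AEs independent of causality and another grades them for all causes. A later sentence of the same section then admits to the safety analysis only events attributed to the intervention.

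**Working it through.** **Denominators.** The planned size is 212, or 106 per group (section 2.6).

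| Arm | Pectin received | Placebo received | At least one dose of the study intervention | Safety set |
|---|---|---|---|---|
| Pectin | yes | – | yes | up to 106 |
| Control | no | no | no, barring crossover | 0 |

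With a control denominator of 0, no risk difference or risk ratio can be formed.

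**Could a control event enter by another route?** Each rule is taken in turn for a control patient:

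1. Safety population (2.7): not met, because no dose was given.
2. AE definition (2.9): not met, because the patient is not receiving the investigational intervention.
3. Events (a) to (d): the clinical wording could be met, but the events still fall under rules 1, 2 and 5.
4. Event (e): cannot be met, because there is no pectin administration from which to count 24 h.
5. Relatedness filter: it states no exposure requirement, but an event cannot be possibly related to a product that was not given. It excludes controls in effect rather than in words.

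**What one arm can show.** The article gives no AE rates, so these counts are assumptions. Exact 95% confidence intervals for events out of 106 are:

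| Events | 95% CI |
|---|---|
| 0 | 0 to 3.4% |
| 5 | 1.5 to 10.7% |
| 11 | 5.3 to 17.8% |
| 21 | 12.7 to 28.7% |

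None of these has a control rate to stand against.

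**What two arms could show.** With 106 against 106, two-sided 5% and 80% power, assumed control rates of 5%, 10%, 20% and 30% allow detection of pectin rates of about 17%, 24.5%, 37% and 49%. Power is limited, but a comparison exists.

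**Why adding controls alone is not enough (illustration only).** Suppose controls were added and the relatedness filter kept. Controls would then score 0 by construction. If the true rate were 10% in both arms, each would have about 0.10 × 106 = 10.6 events. If about half of the pectin events were rated Possible or above, the result would be 5 or 6 against 0.

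- Fisher exact, two-sided: 5 vs 0 gives p = 0.060 and 6 vs 0 gives p = 0.029. If nearly all were so rated, 10 vs 0 gives p = 0.0016.
- Pearson chi-square, the test named in section 2.7 for categorical variables, is 212 × k / (212 − k) for k vs 0. For k = 4 it is 848/208 = 4.08 (p = 0.043). For k = 5 it is 1060/207 = 5.12 (p = 0.024).

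The article does not propose this hybrid analysis. The figures show only why the population and the filter need to change together.

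**The case against.** A reader might infer that no comparison of harm between arms is possible at all. The article does not support that. Section 2.7 compares 28-day mortality by group with Kaplan-Meier curves and a log-rank test, and reports deaths before Day 5 in each arm. Section 2.4.2 lists organ failure, organ support, daily SOFA, the feeding intolerance and gastrointestinal dysfunction scores and the Bristol score as outcomes for the whole trial. This objection stands, and the point is confined to AE and SAE rates.

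A reader might also infer that control AEs are not collected. Table 2 suggests otherwise: it lists both groups under its intervention heading and schedules AEs on Days 1 to 7 and Day 28 without restriction by arm. That stands too, but collection does not bring events into an analysis whose population and filter exclude them.

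A third inference is that the DSMB will see only the pectin arm or only related events. Section 2.8 does not say so. It refers to the cumulative incidence of pre-specified SAEs, section 2.9 sends SAEs to the DSMB with no relatedness condition, and intestinal ischaemia is notified at once. What remains is narrower: aspiration pneumonia is on the DSMB's list, and under definition (e) it could not be counted in controls.

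Finally, the safety population may be loose standard wording that an analysis plan would tidy up. That is possible. But the protocol states the population and the filter outright, so the issue is what it fixes, not what it omits. Stretching the study intervention to cover usual care would contradict section 2.4.4 and would leave definition (e) and the filter as they are.

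**Conclusion.** The point holds for the formal adverse-event analysis. Following the stated rules gives up to 106 pectin patients against 0 controls, so AE and SAE rates cannot be compared between arms. This rests on the literal wording of sections 2.4.4, 2.7 and 2.9 and on no control crossing over to pectin. It needs no assumed event rate.

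Mortality and the secondary organ-failure, organ-support and intolerance outcomes remain comparable. They do not replace a two-arm count of aspiration pneumonia, ileus, tube obstruction or intestinal ischaemia, which the article itself singles out for active monitoring. Separately, the relatedness filter conflicts with the causality-neutral AE definition and the all-cause grading in the same section. The p-values for 4 to 10 events against 0 carry no weight in this conclusion: they describe an analysis that the article does not plan, and the 5 and 6 vs 0 scenarios also rest on an assumed 10% rate.

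**What to change.** - **Safety population:** all randomised participants, analysed by treatment received, both arms included.
- **AE definition:** any untoward event in any randomised participant, recorded by the same rules in both arms.
- **Aspiration pneumonia (e):** arm-neutral clinical and radiological criteria, without pectin timing or attribution to viscosity. Definitions (a) to (d) can stay as worded.
- **Main safety analysis:** all-cause AE and SAE rates by arm with confidence intervals, and the same table supplied by arm to the DSMB. Events rated Possible or above become a secondary tabulation, which removes the conflict within section 2.9.

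The cost is a change of wording in the protocol and in any analysis plan, one eCRF definition, and some additional AE recording in controls. No extra patients or procedures are needed. Recruitment began in February 2024, so the change should be made promptly: control-arm aspiration events not captured under arm-neutral criteria may be hard to recover later.

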#### Primary outcome

2.4.1

The primary outcome of this study is the ratio of EN energy intake to the prescribed target energy on Day 5 after randomization. Patients who died before Day 5 will not be included in the analysis of the primary outcome. Patients who were discharged from ICU before Day5 will be followed up after ICU discharge.

Target energy requirements will be estimated using a simple weight-based equation of 25 kcal/kg of body weight. Body weight used for calculating energy requirements will follow the recommendations of the 2023 ESPEN guideline (2): actual body weight will be used if the body mass index (BMI) is ≤25. For patients with BMI > 25, an adjusted body weight will be applied, defined as:

Adjusted body weight = Ideal body weight + 25% × (actual body weight–ideal body weight). Ideal body weight (kg) will be determined using the formula: 0.9 × height (cm)–100 for males, and 0.9 × height (cm)–106 for females.

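### Scoring every early death as 0% in both arms is a sound composite analysis, but it is not a worst case for the pectin-control difference, and the label should change

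*Protocol article*

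**What the plan says.** The outcome is defined in section 2.4.1: "The primary outcome of this study is the ratio of EN energy intake to the prescribed target energy on Day 5 after randomization". Higher values are better.

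Section 2.7 (Data analysis) removes early deaths from the main comparison: "Patients who die before Day 5 are excluded from the primary analysis as a pre-specified competing event". It then states one sensitivity analysis for them: "A sensitivity analysis will assign these patients an EN delivery ratio of 0% (worst-case assumption"). The patients meant are all those who die before Day 5, so both arms receive 0%. The result is to be shown next to the complete-case result, and early deaths are to be reported for each arm. Administratively missing values are handled separately, by complete-case analysis.

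The planning figures come from section 2.6: "the mean (standard deviation) ratio of EN energy intake to the prescribed target energy on Day 5 was 62.9% (31.1%) in the control group", and "Assuming a minimal clinically meaningful relative increase of 20% in the intervention group".

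**The concern.** A check described as worst-case suggests that the finding has been tested against the assumption least favourable to it. For a claim that pectin raises EN delivery, that assumption penalises deaths in the pectin arm and spares deaths in the control arm. The stated rule penalises both arms equally. Control deaths then pull the control mean down, and the difference can move in pectin's favour.

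At stake is how the result can be read. The article states no other check on excluding deaths. If the difference survives it, or grows under it, the label invites the reader to conclude that the result holds under the most adverse assumption, although no such assumption was examined.

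**Working it through.** **Inputs.** From section 2.6: control mean 62.9%, SD 31.1%, relative increase 20%, 106 per arm. The pectin mean is 62.9 × 1.20 = 75.48%, so the difference is 12.58 points. The article gives no early-death rate, so every death count or rate below is an assumption. Survivor means are held at the planning values, and administratively missing data are ignored.

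**The plan's own figure.** n per arm = 2 × (1.96 + 0.8416)² × 31.1² / 12.58² = 95.9, rounded up to 96. This reproduces the stated 96 per arm, so the inputs are read correctly.

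**Effect under the stated rule.** Let d_p and d_c be the shares of each arm that die before Day 5. With 0% for all of them:

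effect = (1 − d_p) × 75.48 − (1 − d_c) × 62.9

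This exceeds 75.48 − 62.9 exactly when d_c × 62.9 > d_p × 75.48, that is when d_c / d_p > 75.48 / 62.9 = 1.2. If pectin has no effect among survivors, the threshold is 1.0.

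**Why it is not the worst case for pectin.** Raising the score of k_c control deaths from 0% to v% lowers the difference by k_c × v / 106. With at least one control death, any v above 0 therefore gives a smaller pectin effect than the stated rule. For example, with 10 deaths per arm and v = 62.9, the reduction is 629 / 106 = 5.93, and 11.39 − 5.93 = 5.46.

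**Size, in percentage points** (the complete-case difference is 12.58 in every row):

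| Early deaths, pectin / control (of 106 each) | Both 0% (as stated) | Pectin 0%, control 62.9% | Pectin 0%, control 100% |
|---|---|---|---|
| 5 / 5 | 11.99 | 9.02 | 7.27 |
| 10 / 10 | 11.39 | 5.46 | 1.96 |
| 5 / 10 | 14.95 | 9.02 | 5.52 |
| 10 / 5 | 8.43 | 5.46 | 3.71 |
| 6 / 12 | 15.43 | 8.31 | 4.11 |
| 12 / 6 | 7.60 | 4.04 | 1.94 |

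The 6 / 12 row, written out: 75.48 × 100/106 − 62.9 × 94/106 = 71.21 − 55.78 = 15.43. With the same deaths and no effect among survivors, the stated rule gives 62.9 × (12 − 6) / 106 = 3.56.

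**Effect on significance** (normal approximation, assigned values treated as observed). With 10 deaths per arm, p is about 0.02 under the stated rule, 0.23 with control deaths at 62.9%, and 0.68 with control deaths at 100%. With a survivor effect of 8 points, 5 pectin deaths and 10 control deaths, the complete-case analysis gives p of about 0.07. The stated rule gives 10.59 points and p of about 0.025.

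**How often.** Deaths in each arm are taken as Binomial(106, q) with the same q in both arms. The exact probability that the stated rule strictly exceeds the complete-case effect is 37.6%, 32.5% and 28.5% for q = 5%, 10% and 15%. The average effect under the rule is (1 − q) × 12.58, which at q = 10% is 0.90 × 12.58 = 11.3 points.

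**The case against.** The strongest reply is that the parenthesis describes the value given to a patient, and 0% is indeed the lowest possible ratio. A patient who has died receives no EN on Day 5, so 0% is plausible in a way that 62.9% or 100% is not. Arm-specific bounds were designed for values that exist but were not observed. When death is part of the outcome, a mortality difference belongs in the estimate, and chance imbalance is reflected in its standard error. The 3.56-point example is below one standard error: about 4.8 points at 10% early mortality, from √(2 × (0.9 × 31.1² + 0.09 × 62.9²) / 106). A control excess of six or more deaths occurs in only about 10% of trials at that rate, and the mirror split shrinks the effect to 7.60 points. Deaths by arm will be published. Section 2.7 may also lead to a Mann-Whitney test, to which mean differences do not carry over directly.

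Most of this stands. The 0% score is not at fault, and a single bound that gives dead controls a survivor's intake is debatable as an estimate. It is useful only as a deliberately adverse scenario. A reader might infer that the rule favours pectin systematically. It does not: on average it attenuates the effect, and an excess of pectin deaths reduces it clearly. A reader might also infer that the protocol promises to call a positive result robust. It makes no such statement.

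The reply does not rescue the label as a description of the comparison. The rank test changes the figures but not the direction, because raising the control deaths' scores can only move that comparison against pectin. Publishing the deaths shows an imbalance but does not supply the adverse scenario. The absence of a second table would not be a finding on its own in a condensed article. The finding is a stated property that the analysis lacks.

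**Conclusion.** The point holds as one of labelling and interpretation. The stated analysis is a valid composite with death scored as 0%. It is not a worst case for the pectin-control difference, and at the planning means it gives a larger effect than the primary analysis once control early deaths exceed 1.2 times pectin early deaths. With equal true early mortality of 5% to 15%, that happens by chance in roughly 38% to 29% of trials. In the remaining trials, ties apart, the effect shrinks. These frequencies rest on assumed death rates and on survivor means held at 62.9% and 75.48%. That the rule is not the worst case for pectin needs only one control death.

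Severity is minor to moderate. The primary analysis and the sample size are untouched, and deaths per arm will be visible. The documents do not support a claim that the sensitivity analysis is invalid or biased towards pectin.

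**What to change.** In section 2.7, keep the analysis and rename it a composite analysis with death before Day 5 scored as 0%. Add a short tipping-point table in which the value given to early deaths varies separately by arm. Include pectin deaths at 0% with control deaths at the observed control mean, described as a deliberately adverse scenario and not as a plausible estimate. Use the term worst case only for the scenario adverse to pectin. Settle this before allocation is revealed to the analysts.

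The cost is a sentence or two, one extra table and no new data. The stated robustness of a positive result may look less favourable.

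### A Shapiro-Wilk pre-test decides whether the primary outcome is compared by means or by ranks, although the trial is sized on a difference in means

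*Protocol article*

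**What the plan says.** Section 2.4.1 (Primary outcome): "The primary outcome of this study is the ratio of EN energy intake to the prescribed target energy on Day 5 after randomization". This is continuous and cannot fall below 0. No upper cap is stated.

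Section 2.6 (Sample size estimation) takes its control values from an earlier trial, in which "the mean (standard deviation) ratio of EN energy intake to the prescribed target energy on Day 5 was 62.9% (31.1%) in the control group". The effect to be detected is then introduced: "Assuming a minimal clinically meaningful relative increase of 20% in the intervention group". Power, alpha and allocation are those of a standard two-arm comparison, at 80%, 0.05 two-sided and 1:1. The section concludes that "the required sample size is 96 participants per arm".

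Section 2.7 (Data analysis) has a paragraph on the primary outcome. It deals with early deaths and missing data but names no test, model or effect measure. The general paragraph on statistical methods then gives one rule for continuous data: "Normality of continuous variables will be assessed using the Shapiro-Wilk test". Variables judged normal are summarised by mean and SD and compared by Student's t-test. The others are summarised by median and IQR and "compared using the Mann-Whitney U test". The primary outcome is not excepted. Effect estimates with 95% intervals are promised throughout, but the article does not say of what quantity. It also does not say whether normality is judged per arm or on pooled data.

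**The concern.** The minimal clinically meaningful effect is defined as a change in a mean. Under the stated rule, the data decide whether that change is the thing compared. If Shapiro-Wilk rejects, the trial reports medians and a rank test. Mann-Whitney addresses whether values in one arm tend to exceed those in the other, and the difference in medians is a third quantity again. None of these is the 12.58-point mean gain on which the trial was planned.

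Three things are at stake:
- The primary effect measure is not fixed in advance.
- The 80% power was calculated for a comparison of means and does not carry over to the other branch.
- The sensitivity analysis that scores early deaths as 0% adds exact zeros to the same variable. It can therefore fail the normality test when the primary analysis passes. The two results would then differ in test and effect measure as well as in the handling of deaths.

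**Working it through.** **1. Reproduce the plan's figure.** Inputs from section 2.6: control mean 62.9, SD 31.1, relative increase 20%, two-sided alpha 0.05, power 80%, 1:1 allocation.

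- Difference: 0.20 × 62.9 = 12.58 points, so 75.48% in the pectin arm. Standardised: 12.58 / 31.1 = 0.4045.
- n per arm = 2 × (1.960 + 0.842)² × (31.1 / 12.58)² = 95.9, rounded up to 96. This matches the article. The t-based version gives 96.9, so 97; power at 96 is 79.6%.
- An absolute 20-point increase would need only 38 per arm, so the relative reading is the one used.

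The trial is therefore sized on a difference in means. Had Mann-Whitney been the planned test and the data normal, n would be 96 / (3/π) = 100.5 to 97 / (3/π) = 101.6, so 101 or 102 per arm.

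**2. How often would the rule switch to Mann-Whitney?** The article gives no distribution for the ratio, so the shapes below are assumptions, set to means 62.9 and 75.48 and SD about 31.1. Each was simulated with 96 per arm and 2,000 to 3,000 runs. A switch is counted when Shapiro-Wilk gives p < 0.05 in either arm.

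| Assumed shape | Switch | t-test power | Mann-Whitney power |
|---|---|---|---|
| Normal | 10% | 81% | 79% |
| Normal truncated at 0 | 26% | 80% | 78% |
| Normal plus 3% zeros | 34% | 80% | 81% |
| Normal plus 5% zeros | 77% | 78% | 83% |
| Normal plus 8% zeros | 99% | 78% | 89% |
| Beta on 0–150% | 59% | 80% | 79% |
| Beta on 0–120% | 100% | 79% | 80% |
| Beta on 0–100% | 100% | 80% | 97% |
| Normal clipped at 100% | 100% | 76% | 77% |

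Clipping at 100% shrinks the mean difference to about 10.3 points (61.5% to 71.8%), which lowers power for both tests in that row.

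**3. Does the target change?** Where the mean difference stays near 12.6 points, the median difference ranges from about 13 points (normal) to 22 points (beta on 0–100%).

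**4. How the benefit arises also matters.** Two further assumed cases, again with 96 per arm:

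- Gain only from fewer patients with zero delivery: t-test 82%, Mann-Whitney 47%; the tests disagree on significance in 35% of trials. Variants of this case gave 79–95% for the t-test and 43–51% for Mann-Whitney.
- Shift among fed patients with the share of zeros fixed: t-test 70%, Mann-Whitney 94%.

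The first case needs many zeros. If a share p₀ of controls has zero delivery, the mean among the rest is 62.9 / (1 − p₀). Reducing that share to p₁ gains (p₀ − p₁) × 62.9 / (1 − p₀).

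- From 20% to 4%: 0.16 × 78.6 = 12.6 points.
- From 17% to 0.4%: 0.166 × 75.8 = 12.6 points.
- From 10% to none: 0.10 × 69.9 = 7.0 points, short of the planned effect.
- From 12% to none: 0.12 × 71.5 = 8.6 points, also short.

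**5. Type I error.** Choosing the test by Shapiro-Wilk gave 4.9% to 5.7% across five shapes. The simulation standard error at 3,000 runs is √(0.05 × 0.95 / 3000) = 0.4 points, so this is compatible with 5%.

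**The case against.** The rule is conventional, both branches are valid tests stated in advance, and the error rate holds. The article is condensed, and an analysis plan that is not shown may name the primary model. These points limit the harm, but they do not remove it. The article states a rule for all continuous variables without exempting the primary outcome, so this is a stated choice and not a detail left open.

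Four stronger readings are tempting, and the documents support none of them.

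- **That Mann-Whitney will be used.** The rule is conditional, and the switch rate runs from about 10% to 100% depending on an unknown shape.
- **That the ratio piles up at 0 and near 100%.** Only the floor at 0 is certain. Early deaths, an obvious source of zeros, are left out of the primary analysis. Postpyloric feeding after gastric intolerance is still enteral, so intolerance need not mean zero delivery. Zeros remain possible through a switch to PN or to full oral intake.
- **That pectin is expected to work by preventing complete EN failure.** The Introduction speaks of less retrograde flow and fewer interruptions caused by reflux, which fits partial gains as well. The 47% figure rests on an extreme version of the other mechanism.
- **That the rule costs power in general.** Mann-Whitney was weaker in some shapes and stronger in others.

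**Conclusion.** The point holds as a defect in how the primary comparison is fixed. The test and the effect measure depend on a normality test, while the sample size and the minimal important effect are stated for a mean difference of 12.58 points. With the floor only 62.9 / 31.1 = 2.0 SD below the control mean, a switch to ranks is a real possibility, and it becomes likely with roughly 5% or more exact zeros or with a ceiling near 100–120%. Mann-Whitney power then lies anywhere from about 47% to 97%, and in some settings the choice of test alone would decide significance. All switch rates and power figures rest on assumed distributions; the article gives only a mean and an SD. Neither a general loss of power nor a material inflation of type I error is shown.

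**What to change.** Exempt the primary outcome from the normality pre-test. State in section 2.7 that it is analysed as the difference in mean Day-5 ratio with a 95% CI, by an unequal-variance t-test or a linear model with robust standard errors, whatever a normality test shows. Apply the same analysis to the sensitivity analysis that scores early deaths as 0%. Keep Mann-Whitney as a sensitivity analysis.

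The cost is about one sentence, added before unblinding, with no new data and no change in sample size: 96 per arm still gives 80.0% power by the normal approximation, or 79.6% by the t-test. The downside is that a mean comparison is less powerful than Mann-Whitney if the effect is a pure shift among fed patients with an unchanged share of zeros (70% against 94% in the case simulated).
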